### Statistical methods

The main analysis for primary and secondary endpoints will be based on multilevel mixed models, including as covariates the baseline value of the dependent variable, the severity of the patient and the professional’s level of baseline knowledge. First level variables will be those corresponding to each measurement throughout follow-up (related time measurements), second level includes patient variables and third level variables correspond to hospital (cluster). The effect that identifies the intervention arm will be considered fixed for the different hospitals, whilst the intercept will be considered random. The model will also include an interaction term between arm and month, allowing for differences in the intervention effect between follow-up assessments [36]. The adjusted estimated mean will be calculated for each moment of follow up compared to baseline. To accommodate missing values in the effect analyses, the multiple imputation procedure in STATA V15.0 will be used [37]. This procedure saves cases for analysis and can be considered as an intention-to-treat analysis. Differences will be considered statistically significant if *p*-value < 0.05.

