### Random assignment

Allocation by cluster was performed with hospitals as randomization units. After selection of professionals, an investigator blinded to hospital identity randomly assigned two hospitals to the intervention group and two hospitals to the control group by simple generation from a list of random numbers.

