Every three months during the 18-month follow-up, participating rheumatologists receive feedback on their clinical management of SLE patients consisting of an information sheet displaying a personalized graphical summary of relevant process indicators compared to mean results obtained by their own services. The document is received by email and graphically displays combined indicators, periodically generated by automated audit of electronic clinical records of all SLE patients (whether or not included in the study).

Process indicators displayed include: 1) prescription of antimalarials to SLE patients 2) prescription of antimalarials in particular to pregnant SLE women; and 3) prescription of glucocorticoids (prednisone, deflazacort and methylprednisolone) according to SLE-CPG recommendations. For every indicator displayed on the sheet, mean reference values obtained from all rheumatologists at the same hospital are used as dynamic comparators.

Participating rheumatologists assigned to the control group continue usual practice and do not receive any intervention.

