##### Knowledge of professionals about SLE management

Knowledge level of recommendations for SLE management formulated in the SLE-CPG [10] will be assessed by mean of a 10-question test developed ad hoc administered to rheumatologists. Responses to questions scored 1 point if correct or 0 point if incorrect. Thus, possible scores ranged from 0 to 10. This instrument will only be administered to rheumatologists of the intervention group before and after the educational group programme, and at 18 months.

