#### Additional measures

Sociodemographic data will be collected at baseline from patients and rheumatologists. Professionals will be asked about their age, sex and professional profile (years in practice, degree of expertise in SLE, etc.), while patients will be asked about their sex, age, education level, occupation, employment situation, marital status, family living status (alone or accompanied), and age at SLE diagnosis.

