### Data management

Data collection is managed by means of an electronic case report form designed for this study and complemented with patient questionnaires self-completed at baseline, and at 9 and 18 months by phone. Information from professionals is obtained by means of self-reported questionnaires.

On receipt of their consent forms, all participants (professional and patient) is assigned a code which will link their data to a master-sheet which will contain participants’ demographic details and location. The mastersheet will be kept secure and confidential by the project coordinator in a password-protected file in the Project data management system. All data for the evaluation of the project will be identified by the participants’ code only. This is so that the data can be kept confidential but can be re-identified to enable appropriate grouping and analysis in the case studies at the end of the study.

Hard copies of all consent forms and questionnaires will be stored in locked filing cabinets in the Evaluation Service of the Canary Health Service (or password-protected folder if in soft copy form) up to 5 years after finishing the trial.

The planning of information collection for every outcome measured throughout the project is shown in Table 1.

**Table 1 Tab1:** Outcome measurements according to time points of collection

Time point	Outcomes measured on patients	Outcomes measured on rheumatologists
T1 (baseline)^a^	Demographic data SLAQ [29]; EQ-5D-5L [30]; LupusQoL [31]; SDM-Q-9^c^ [32]	Demographic data; professional profile; Adherence to recommendations; LatConII^d^ [34, 35]; Knowledge test^d^
T2 (9 mo)^b^	SLAQ [29]; Health care utilization and productivity losses	
T3 (18 mo)^b^	SLAQ [29]; EQ-5D-5L [30]; LupusQoL [31]; Health care utilization and productivity losses	Adherence to recommendations; LatConII [34, 35]; Knowledge test

*Abbreviations*: *LatConII* Leeds Attitude Towards Concordance II Scale, *LupusQoL* Systemic Lupus Erythematosus Quality of Life questionnaire, *SDM-Q-9* Shared Decision-Making questionnaire, *SLAQ* Systemic Lupus Erythematosus Activity Questionnaire, *mo* months

^a^Self-reported face to face

^b^Self-reported by telephone

^c^Also after each consultation during study follow-up

^d^Before and after the educational group programme

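### The main between-arm model adjusts for the professional's baseline knowledge, but the knowledge test is given only in the intervention arm, so the covariate is missing by design for all controls

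*Protocol article*

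**What the plan says.** All references are to the protocol article.

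- **Statistical methods**, on scope: "The main analysis for primary and secondary endpoints will be based on multilevel mixed models". On covariates: "including as covariates the baseline value of the dependent variable, the severity of the patient and the professional’s level of baseline knowledge". On missing data: "To accommodate missing values in the effect analyses, the multiple imputation procedure in STATA V15.0 will be used".
- **Knowledge of professionals about SLE management** describes an ad hoc test scored 0 to 10, the only knowledge measure in the document, and restricts it: "This instrument will only be administered to rheumatologists of the intervention group before and after the educational group programme, and at 18 months".
- **Data management, Table 1** lists the knowledge test for rheumatologists at baseline without naming an arm. Its footnote gives the timing as "Before and after the educational group programme".
- **Intervention**, on controls: "Participating rheumatologists assigned to the control group continue usual practice and do not receive any intervention".
- **Additional measures**, on other baseline data from rheumatologists: "Professionals will be asked about their age, sex and professional profile (years in practice, degree of expertise in SLE, etc". No arm restriction is stated there.
- **Random assignment**: an investigator "randomly assigned two hospitals to the intervention group and two hospitals to the control group".

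**The concern.** A covariate in a between-arm model has to be observed in both arms. Here one section makes baseline knowledge part of the main model, and another rules out measuring it in the control arm. This is not a detail left for an analysis plan to fill in: the article itself fixes both halves, and they conflict.

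The primary comparison is at stake. With two hospitals per arm, the rheumatologists in the two arms could differ in prior knowledge by chance, which is presumably why the covariate was chosen. If the text stands, someone will have to decide whether to drop, replace or impute it. Unless that is settled before unblinding, the choice could be made with the results in view.

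**Working it through.** **1. The plan's own figure.** Inputs from Sample size calculation: effect size 0.3, SD 8, ICC 0.01, power 80%, significance 5% (taken as two-sided), 418 patients, 20 professionals.

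- Per arm without clustering: 2 × (1.96 + 0.8416)² / 0.3² = 2 × 7.849 / 0.09 = 174.4, so 175, or 350 in total.
- Patients per rheumatologist: 418 / 20 = 20.9. Design effect: 1 + (20.9 − 1) × 0.01 = 1.199.
- 350 × 1.199 = 419.65, against 418 stated. The figure reproduces to within 0.4%.
- Design difference: 0.3 × 8 = 2.4 SLAQ points.

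The point does not depend on 418; the figure only gives the scale.

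**2. Who has the covariate.**

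| Source | Intervention rheumatologists | Control rheumatologists |
|---|---|---|
| Knowledge section | tested before and after the programme, and at 18 months | excluded by the word *only* |
| Table 1 footnote | tied to the educational programme | no programme to attend |
| Statistical methods | covariate required | covariate required |

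If the arms are equal in size, 418 / 2 = 209 control patients lack the covariate by design. (The abstract gives 412 patients, which would make it 206.)

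**3. Complete-case fit.** Take the fixed effects as intercept, arm, month (18 against 9), arm × month, baseline value and knowledge: 6 columns. Severity is left out because it does not alter the argument. Only intervention records remain, so arm = 1 in every row. The arm column then equals the intercept and arm × month equals month, so the rank is 6 − 2 = 4. A constructed data set of 4 hospitals × 5 rheumatologists × 21 patients × 2 visits = 840 records confirmed this: 420 records remained, all from the intervention arm, with rank 4. The arm effect and its interaction with month are not estimable.

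**4. Multiple imputation.** With slope *b* for knowledge, the adjusted arm effect is approximately

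(mean Y_I − mean Y_C) − b × (mean K_I − mean K_C).

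No control K is observed, so mean K_C comes wholly from the imputation model. If arm is in that model, its coefficient is not identified. If arm is left out, controls are taken to resemble intervention rheumatologists given the other variables. In the simplest case, where mean K_C is set equal to mean K_I, the correction is b × 0 = 0 and the result is the estimate unadjusted for knowledge. In neither case can the data reveal a real difference in knowledge between the arms.

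**5. How much imbalance could go uncorrected.** SD 8 and ICC 0.01 give a between-cluster SD of 8 × √0.01 = 0.8 SLAQ points. Assume the extreme case, in which knowledge explains all of that variation. There are 2 × 5 = 10 rheumatologists per arm. One standard deviation of the chance difference in mean knowledge, in units of the knowledge SD, is:

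- rheumatologists independent: √(1/10 + 1/10) = 0.447, giving 0.447 × 0.8 = 0.36 points, or 0.36 / 2.4 = 15% of the design difference;
- all rheumatologists in a hospital alike: √(1/2 + 1/2) = 1, giving 0.8 points, or 0.8 / 2.4 = 33%.

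If knowledge explains less of the between-cluster variation, or baseline SLAQ already absorbs part of it, the figures are smaller.

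**The case against.** **The model can still be fitted.** A reader might infer that the primary analysis cannot be run at all, or that its arm effect would rest on invented numbers. The documents do not support that. Multiple imputation is planned and software would return an estimate. Randomisation makes a pre-intervention covariate independent of arm in expectation, and step 4 shows that a neutral imputation simply gives back the estimate unadjusted for knowledge. Imputation therefore need not distort the effect. What stands is that the adjustment cannot do what it is there for, and that the result depends on an untestable assumption.

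**Knowledge may mean something else.** Statistical methods does not name the test, Table 1 shows it at baseline without an arm, and degree of expertise is asked of professionals without restriction. The authors may have meant a measure held in both arms. This reading is possible but weaker. The knowledge section is explicit, the table footnote agrees with it, and expertise is described as part of the professional profile. If expertise was meant, the covariate sentence still needs correcting.

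**Reach across endpoints.** A reader might infer that every secondary endpoint is affected. LATCon II and the knowledge test are measured only in the intervention arm. For LATCon II the covariate is available by design, and for the knowledge test it is the outcome's own baseline. Neither is harmed.

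**Severity.** A reader might also infer that the patient-severity covariate is uncollected, because Additional measures and Table 1 do not list it. That does not follow. One covers sociodemographic data and the other outcome measurements, clinical records and an electronic case report form are also data sources, and an article may leave the definition to a fuller document.

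**Conclusion.** The conflict is real and sits in the prespecified primary model. Baseline knowledge is missing by design for all control rheumatologists and their patients, which is about half of the 418 if the arms are equal. That split is an assumption, since only the total is given and hospitals are the units allocated. Complete intervention-arm scores are not assured either.

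A complete-case fit gives no arm effect. An imputed fit gives one that cannot correct imbalance in knowledge. Under the extreme assumption of step 5, one standard deviation of such imbalance is worth 0.36 to 0.8 SLAQ points against a design difference of 2.4. The more practical harm is that the primary analysis has no single executable specification. The conclusion covers SLAQ and the secondary endpoints compared between arms, and no others. It should be settled before unblinding.

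**What to change.** Before unblinding, reconcile Statistical methods with the knowledge section in one of two ways:

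1. Remove baseline knowledge from the between-arm models.
2. Replace it with a named professional-level covariate collected at baseline in both arms. Years in practice and degree of expertise in SLE, both listed in Additional measures, are candidates.

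State that the change applies to SLAQ and to the secondary endpoints compared between arms. If control rheumatologists did in fact take the test at baseline, correct the knowledge section and Table 1 instead. Otherwise, with recruitment reported complete and the intervention under way, a true control baseline score may no longer be obtainable.

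The cost is one sentence. It needs no new data and no change in sample size, since the calculation does not use the covariate.

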### Intervention

Participating rheumatologists assigned to the intervention group receive a multicomponent intervention designed according to the conceptual framework of behavioural change [23, 24] and person centred care model [25, 26], constituted by the following components: A) educational group programme, B) continuous support by means of an automated decision aid tool embedded into the electronic clinical record for patients included, and C) periodic feedback on process and outcome measures for all SLE patients seen. Although this set of interventions applies only to professionals, some outcome measures will be ascertained among patients included.
A)Educational and training group programme

This consists of 6 h face-to-face group training divided into two sessions, 3 months apart. Contents of the first session are designed to attain the following objectives: 1) update evidence-based clinical knowledge on SLE management according to the contents of the SLE-CPG [10] and 2) develop skills to improve communication and negotiation abilities in the context of the person-centred care model [26] and shared decision making [25]. A set of short video-films and role-playing exercises representing different types of complex sham patients are used to deliver this intervention. The aim is to train professionals to: 1) foster a climate of participation and establish clear and efficient communication; 2) elicit the patient’s concerns and preferences about possible decisions; and 3) promote shared decision making based on the best evidence, professional experience and the patient’s values and preferences in those decisions where either considerable uncertainty or several proven alternatives exists. The first part of the session is led by the clinical leader of the development of the SLE-CPG [10], a recognized rheumatologist expert in SLE, while the second part is led by two psychologists with proven expertise in patient-centred care methods and communication skills. The session also includes an explanation and training on use of the electronic decision aid tool (see below) led by the study’s principal researcher.

The second session (3 h) is designed to reinforce the skills acquired on the patient-centred care model and shared decision making [21, 22].

Both sessions are video-recorded to standardize training and to ensure intervention reliability [27].
B)Electronic decision support (EDS) system

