#### Secondary outcomes

##### Adherence of professionals to recommendations

Recommendations expected to have a greater impact on patients’ health which are those related to prescription of antimalarials and glucocorticoids will be analyzed. Degree of professional adherence to recommendations will be determined through data collection from clinical records at baseline and 18 months of follow-up in terms of percentage of patients with adequate treatment according to SLE-CPG recommendations. The appropriateness of treatments prescribed will be assessed and treatments will be classified as adequate (agree with antimalarials and glucocorticoids choice, dosage, dosing interval and duration of treatment) or inadequate.

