### Sample size calculation

A total of 418 patients and 20 professionals (5 per hospital) will be required to detect an effect size of 0.3 (small) in the activity of the SLE (SLAQ) assuming a standard deviation of 8 and an intra-class correlation coefficient (ICC) of 0.01 with a power of 80% and a level of statistical significance of 5%.

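### The stated mixed model has no rheumatologist level, so clustering by clinician can drop out of the arm comparison when the four-hospital variance is estimated at zero

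*Protocol article*

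**What the plan says.** The Statistical methods section applies one family of multilevel models to the primary and secondary endpoints. Repeated measurements form the first level, and above them "second level includes patient variables and third level variables correspond to hospital (cluster"). On the effects it says: "The effect that identifies the intervention arm will be considered fixed for the different hospitals, whilst the intercept will be considered random". The only clinician-level term is a fixed covariate, the professional's baseline knowledge.

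The Random assignment section makes the hospital the allocated unit ("Allocation by cluster was performed with hospitals as randomization units"), two per arm. The Intervention section says of the training, decision support and feedback: "Although this set of interventions applies only to professionals".

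The Sample size calculation section reads "A total of 418 patients and 20 professionals (5 per hospital) will be required to detect an effect size of 0.3 (small"), "assuming a standard deviation of 8", with an ICC of 0.01, 80% power and 5% significance. It does not say whether the ICC refers to rheumatologists or hospitals.

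Adherence, a secondary outcome, is expressed as the "percentage of patients with adequate treatment according to SLE-CPG recommendations".

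**The concern.** Patients belong to about 20 rheumatologists, who belong to four hospitals. The treatment is aimed at the middle layer, and the sample size arithmetic appears to rest on it, but the stated model passes from patient straight to hospital. If patients of the same rheumatologist have correlated outcomes, that variance contributes to the uncertainty of the arm comparison and must enter its standard error somewhere.

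In the stated model it can enter only through the hospital intercept. That variance is estimated from four hospitals with two residual degrees of freedom once arm is fitted. When the estimate falls to zero, the model treats all patients as independent and the clinician variance is lost. What is at stake is false-positive error for the arm effect, above all for an outcome that reflects prescribing behaviour.

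**Working it through.** **1. Reproducing the stated sample size.** Inputs from the Sample size calculation section: standardised effect 0.3 (0.3 × 8 = 2.4 SLAQ points), SD 8, ICC 0.01, 80% power, 5% significance. The article does not state sidedness; two-sided is assumed.

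- Unclustered total: 4 × [(1.960 + 0.842)/0.3]² = 348.8.
- With k clusters: N = n(1 − ICC)/(1 − n·ICC/k), where n = 348.8.
- k = 20 rheumatologists: 348.8 × 0.99/(1 − 0.1744) = 418.3, which matches 418.
- k = 4 hospitals: 348.8 × 0.99/(1 − 0.8721) ≈ 2,700, which does not.

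So the clinician is the cluster by arithmetic, though not in words. At 418/20 = 20.9 patients per rheumatologist the design effect is 1 + 19.9 × 0.01 = 1.199.

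**2. What happens when the hospital variance is estimated at zero.** The model's standard error then omits the design effect, so a nominal 5% z test rejects with probability 2 × [1 − Φ(1.96/√DE)]:

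- Clinician ICC 0.01, DE 1.199: 7.3%.
- Clinician ICC 0.05, DE 1 + 19.9 × 0.05 = 1.995: 16.5%.

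**3. How often that happens, and the overall effect.** Null trials were simulated with 4 hospitals × 5 rheumatologists × 21 patients, one Gaussian follow-up measure, no true hospital variance and a z test. With M = 105 patients per hospital, the variance of the arm difference is λ/M. Under the hospital-only model λ is the between-hospital mean square, or the pooled mean square if the hospital variance would be negative. Adding the rheumatologist level means that λ falls back first on the between-clinician mean square.

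| Clinician ICC | Estimator | Hospital variance estimated at zero | Type I error, stated model | With rheumatologist level |
|---|---|---|---|---|
| 0.01 | REML | 56% | 5.1% | 3.9% |
| 0.01 | ML | 81% | 6.6% | 5.4% |
| 0.05 (assumed) | REML | 39% | 9.5% | 4.8% |
| 0.05 (assumed) | ML | 63% | 13.4% | 7.1% |
| 0.10 (assumed) | REML | 28% | 12.7% | 4.9% |
| 0.10 (assumed) | ML | 48% | 18.7% | 7.3% |

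Repeat runs agree to within about 0.2 percentage points. The overall REML figure at ICC 0.01 is near nominal because two groups of trials offset each other: 7.4% rejection in the 56% with a zero estimate and 2.3% in the rest, so 0.56 × 7.4 + 0.44 × 2.3 ≈ 5.2%.

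**4. If hospitals truly differ.** With hospital ICC 0.01 as well (assumed; REML, z), error is about 10.6% without the rheumatologist level and 9.1% with it at clinician ICC 0.01, and 12.8% and 8.1% at clinician ICC 0.05. The extra level helps but does not restore 5%.

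**5. With a t reference on 2 df.** Rejection is below 2% in every setting examined, with or without the extra level.

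**The case against.** The strongest reply is that the hospital is the randomised unit and is in the model. A reader might infer from the missing level that the arm's standard errors are too small in general. The documents do not support that: a hospital intercept estimated away from zero already carries the clinician variance, so the shortfall arises only when it is estimated at or near zero.

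Nor can one infer that the SLAQ analysis is seriously compromised. At the only ICC in the article, 0.01, the stated model under REML is closer to nominal overall (5.1%) than the model with the extra level (3.9%). The ICCs of 0.05 and 0.10 are assumptions.

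The inflation also depends on a z reference. The article names none, and under a 2-df reference there is no inflation for the level to cure.

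On adherence, the simulation is Gaussian with no baseline adjustment, whereas adherence is binary per patient and the model adjusts for the baseline value, which would remove part of any stable clinician difference. Table 1 lists adherence among outcomes measured on rheumatologists; if it is analysed per rheumatologist, a level between patient and hospital would not apply.

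All of this stands, and it limits the size of the point. It does not explain why the level on which the sample size arithmetic depends is absent from the stated model. The baseline knowledge covariate is no substitute, because the Knowledge of professionals section gives that test only to intervention-group rheumatologists.

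**Conclusion.** The point holds in a conditional form. The stated model omits a known clustering level, the one at which the intervention acts and the only one whose count reproduces 418. The arm's standard error can be too small when the hospital variance is estimated at zero, which is common with four hospitals.

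With a z test and no true hospital variance, the consequence for SLAQ at the stated ICC is small: about 1.2 percentage points of type I error under either estimator. It is material only at a larger clinician ICC. At 0.05 the level removes 4.7 points under REML (9.5% to 4.8%) and 6.3 under ML (13.4% to 7.1%). That ICC is an assumption, most plausible for prescribing adherence analysed per patient. The figures also assume balanced hospitals and a single Gaussian follow-up measure.

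The change is worth making because it is cheap and aligns the analysis with the sample size basis. It is not evidence that the primary analysis is invalid.

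**What to change.** In Statistical methods, define four levels: measurement, patient, rheumatologist and hospital, with a random intercept for rheumatologist. Apply this to SLAQ and the patient-level secondary outcomes, including adherence if it is analysed per patient. Keep the hospital intercept, since the hospital was randomised. State in the sample size section which unit the ICC of 0.01 refers to.

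The cost is one random-effect term and no extra patients. Rheumatologists recruit their own patients, so the link should be available. The downsides are slightly wider intervals, possible convergence problems, and a more conservative test if a 2-df reference is also used. Two hospitals per arm remain a separate problem that needs its own small-sample reference; this change does not resolve it.

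### With two hospitals per arm and no small-sample inference named, the random-hospital-intercept model at p<0.05 can exceed its 5% error rate, by an amount set by a hospital ICC the protocol does not give

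*Protocol article*

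**What the plan says.** Under Random assignment, an investigator "randomly assigned two hospitals to the intervention group and two hospitals to the control group". Under Statistical methods, the main analysis of primary and secondary endpoints is a three-level mixed model: repeated measurements, patients, then hospitals. On the arm effect it says "The effect that identifies the intervention arm will be considered fixed for the different hospitals, whilst the intercept will be considered random". The baseline value of the outcome is one of the covariates, and there is an arm-by-month interaction. The decision rule is "Differences will be considered statistically significant if *p*-value < 0.05". The section does not say whether estimation is by ML or REML, which reference distribution is used, or whether any correction is made for the small number of hospitals.

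Under Sample size calculation, the target is 418 patients and 20 professionals, sized for a SLAQ effect of 0.3 SD at 80% power and the 5% level. The calculation is made "assuming a standard deviation of 8 and an intra-class correlation coefficient (ICC) of 0.01". Which level that ICC belongs to is not stated.

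**The concern.** Every patient in a hospital is in the same arm, so the arm effect is a comparison of two pairs of hospitals. The between-hospital variance that enters its standard error is estimated from four hospitals, less one degree of freedom per arm, which leaves 2. Two things follow if the estimate is referred to a normal distribution. The critical value of 1.96 ignores how poorly that variance is known. And the variance estimate is often exactly zero, after which all patients are treated as independent.

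A SLAQ difference declared significant could then be an ordinary chance difference between two pairs of hospitals, and its confidence interval would be too narrow. The same model is planned for the secondary endpoints.

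**Working it through.** **Inputs.** Four hospitals, two per arm (Random assignment). 418 patients, 20 professionals, SD 8, effect size 0.3 (0.3 × 8 = 2.4 SLAQ points), ICC 0.01, power 80%, 5% level (Sample size calculation; taken as two-sided). Per hospital 418/4 = 104.5 patients; per professional 418/20 = 20.9.

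**1. The plan's own sample size.** Without clustering, 2 × (1.960 + 0.842)² × 8² / 2.4² = 174.4, so 175 per arm and 350 in all.
- Professionals as clusters: design effect 1 + (20.9 − 1) × 0.01 = 1.199; 350 × 1.199 = 420. This matches 418 closely (the Abstract gives 412).
- Hospitals as clusters: design effect 1 + (104.5 − 1) × 0.01 = 2.035; 350 × 2.035 = 712. Solving with only two hospitals per arm gives 2,772.

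So 0.01 appears to have been applied to professionals, and no hospital-level ICC is given.

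**2. Error rate of the large-sample test.** Null trials were simulated with 4 hospitals × 104 patients and a random hospital intercept, 400,000 per setting. With equal hospital sizes the fit has a closed form:
- MSB = 104 × (sum of squared deviations of hospital means from their arm mean) / 2 for REML, or / 4 for ML.
- If MSB exceeds the within-hospital mean square, the variance of the arm difference is MSB/104. Otherwise the hospital variance is set to zero and the pooled patient variance is used.
- Reject if |difference| / SE > 1.96.

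| Hospital ICC | REML | ML | t-test on hospital means, 2 df |
|---|---|---|---|
| 0 | 3.7% | 4.7% | 5.0% |
| 0.001 | 4.6% | 5.9% | 5.0% |
| 0.005 | 7.2% | 9.7% | 5.0% |
| 0.01 | 9.8% | 13.7% | 5.0% |
| 0.02 | 12.8% | 18.9% | 5.0% |

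Repeat runs differ by 0.1 to 0.2 points. At ICC 0.01 the hospital variance is estimated as zero in 39% (REML) or 62% (ML) of null trials.

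**3. Closer to the planned model.** Using both follow-ups (9 and 18 months), a patient intercept and arm-by-month, with within-patient correlation assumed at 0.5 or 0.7, the 18-month contrast at ICC 0.01 has an error rate of 9.5–9.9% (REML) and 13.2–13.5% (ML), from 12,000 trials per setting. The result is not an artefact of the simpler model.

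**4. Power of the 2-df test with 418 patients.** SE of the arm difference = 8 × √(ICC + (1 − ICC)/104.5).
- ICC 0.01: SE = 1.116; non-centrality 2.4/1.116 = 2.15; critical value 4.303; power 24%. The normal-theory formula with the same SE gives Φ(2.15 − 1.96) = 58%.
- ICC 0: SE = 0.783; non-centrality 3.07; power 40%.

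At ICC 0.01 and the true SE, the 95% CI half-width is 4.303 × 1.116 = 4.8 SLAQ points, against 1.96 × 1.116 = 2.2 with a normal critical value.

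**5. A tempting shortcut.** Keeping the zero-bounded REML standard error and replacing 1.96 by 4.303 rejects in only about 0.1% of null trials at ICC 0.01. It is not equivalent to the t-test on hospital means.

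**The case against.** The strongest reply is that the article names no test. The reference distribution is commonly left to the analysis plan, which is not shown, and a small-sample method may be specified there. That stands: the inflation is conditional on a large-sample test. Such a method would not, however, rescue the stated 80% power, because the sample size shows no sign of a 2-df test.

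Second, a reader might infer that 0.01 is the hospital ICC and that the plan's own assumption therefore implies a 10–14% error rate. The documents do not support this, since 418 reproduces with professionals as clusters. At a hospital ICC of 0.001 or below, the Wald test runs between about 3.7% and 5.9%, which is no material inflation. The relevant ICC is also the one left after adjustment for baseline SLAQ and severity, and it could be smaller. Equally, nothing in the article shows that it is negligible.

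Third, from "The adjusted estimated mean will be calculated for each moment of follow up compared to baseline" a reader might infer that baseline SLAQ enters as an outcome, so that a time-constant hospital intercept cancels from the 18-month change. The same section lists the baseline value as a covariate and describes arm-by-month as allowing for differences between follow-up assessments. The sentence is at most ambiguous about reporting.

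Fourth, four hospitals allow only six allocations, so an exact randomisation test could not give a two-sided p below 2/6 = 0.33. No such test is planned, so this illustrates how little the design can show and is not an error in the analysis.

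**Conclusion.** The point holds conditionally. A random-hospital-intercept model at p<0.05, with two hospitals per arm and no small-sample inference named, does not by itself secure a 5% error rate. Under a large-sample Wald test the rate ranges from slightly below 5% at hospital ICC 0 to 9.8% (REML) or 13.7% (ML) at 0.01, and is higher above that. The figures assume equal hospital sizes, normal hospital effects and no covariates; covariates may change the residual hospital variance but do not add hospitals.

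It would go too far to say that the planned test is known to be inflated, or to quote 10–14% as the trial's error rate: neither the test nor the hospital ICC is stated. The matter still needs settling before unblinding, because it governs the primary p-value and interval and because a valid 2-df test leaves power far below 80% at any hospital ICC.

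**What to change.** - Before unblinding, base the primary p-value and 95% CI on the four hospital mean 18-month SLAQ scores, adjusted for patient-level baseline covariates (baseline SLAQ, severity), compared between arms with a t distribution on 2 df. Leave professionals' baseline knowledge out of this adjustment: the Outcome measures section gives that test only to the intervention group.
- Keep the mixed model as supportive, with baseline SLAQ as a covariate only and 9 and 18 months as outcomes. Reword the sentence on comparison with baseline accordingly.
- Report the estimated hospital ICC.
- Do not offer the zero-bounded REML standard error with a 2-df critical value as an equivalent.
- Restate the power: about 24% at hospital ICC 0.01 and about 40% at ICC 0, for effect size 0.3 with 418 patients and SD 8. Say to which level the 0.01 applies.

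The change needs only a pre-specified paragraph and a little code. Data collection is ongoing, and the analyst is to stay blind until the trial ends, so there is still time. The statistical cost is real: much wider intervals, a less favourable p-value, and a t-test whose normality and equal-variance assumptions cannot be checked with two hospitals per arm. Recruitment is complete, and more patients in the same four hospitals would not add degrees of freedom.
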